**Methods:**

Changes in the total UPDRS scores from baseline to the 8^th^, 24^th^, 48^th^, and 72^nd^ weeks, and after the 8^th^ week, will be evaluated. The primary endpoint of the efficacy of this treatment in PD is the change in the total UPDRS score from baseline to the 72^nd^ week. The changes in UPDRS part II, UPDRS part III, each UPDRS score, PD Questionnaire-39 (PDQ-39), and the modified Hoehn and Yahr stage at these same time-points, as well as the duration until the protocol is finished because additional levodopa is required or until the disease progresses, will also be analyzed. Adverse events and screening laboratory studies will also be examined. Participants in the hydrogen water group will drink 1000 mL/day of H_2_ water, and those in the placebo water group will drink normal water. One-hundred-and-seventy-eight participants with PD (89 women, 89 men; mean age: 64.2 [SD 9.2] years, total UPDRS: 23.7 [11.8], with levodopa medication: 154 participants, without levodopa medication: 24 participants; daily levodopa dose: 344.1 [202.8] mg, total levodopa equivalent dose: 592.0 [317.6] mg) were enrolled in 14 hospitals and were randomized.

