## Methods

A placebo-controlled, randomized, double-blind, parallel-group (1:1) clinical multi-center trial was organized by the Department of Neurology of Juntendo University School of Medicine in accordance with Consolidated Standards of Reporting Trials (CONSORT) guideline. Fourteen hospitals are involved as trial centers. This trial was advertised in posters and on homepages of our clinic, and participants had to declare their intentions to participate voluntarily. The inclusion criteria required that the participants have a diagnosis of PD according to the United Kingdom Brain Bank criteria [8]. All the participants should have a modified Hoehn and Yahr staging (H & Y stage) in the on-phase between 1 and 4. For 8 weeks prior to establishing the baseline, the participants’ antiparkinsonian drugs were not changed. None of the participants have dementia (MMSE < 25) or dysphagia for water. Outpatients are preferred over admitted patients. The participants are to be older than 20 years. The exclusion criteria included the following: parkinsonism due to diseases other than PD, the presence of other serious diseases, malignant tumor(s), or adverse events caused by drugs.

The clinical study is registered at UMIN clinical trial registry (UMIN-CTR) UMIN000010014 (February 13, 2013). The Ethics Committee of the Juntendo University School of Medicine approved this study in February 2013, as did the ethics committees of other centers, and all participants provided signed informed consent forms.

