### Randomization and blinding

The enrolled participants have been assigned using a stratified randomization method according to their age and if they were receiving levodopa. The assignments were made by [name] The participants and those assessing outcomes will remain blinded until all the participants have finished the protocol.

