**Fig. 1 Fig1:**
[figure not shown]
Schedule of enrolment, intervention, and assessment. Study period of enrolment, allocation, and baseline may coincide. It is approximately 1 week to 10 days from allocation to the first day to start shipping the water. *1: Unified Parkinson’s Disease Rating Scale. *2: Parkinson’s Disease Questionnaire-39

The changes in UPDRS part II, UPDRS part III, each UPDRS score, PD Questionnaire-39 (PDQ-39), and the H & Y stage at these same time-points, as well as the duration until the protocol is finished because additional levodopa is required or until the disease progresses, will also be analyzed. Adverse events and screening laboratory parameters (total protein, albumin, alkaline phosphatase, aspartate transaminase, alanine transaminase, serum urea nitrogen, calcium, chloride, creatinine, glucose, lactate dehydrogenase, potassium, sodium, creatinine kinase, uric acid, choline esterase, LDL-cholesterol, HDL-cholesterol, and triglyceride levels) will also be examined.

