### Statistical analysis

We calculated that a minimum of 95.4 participants need to be enrolled to detect a 5-point difference in the UPDRS scores between the 2 groups, with a standard deviation of the mean difference of 10, and a 2-sided alpha level of 0.05 and 80 %. Assuming a 35 % dropout, 96 participants will be required in total. A period of 72 weeks’ follow-up is a relatively long-term clinical trial in PD; hence, we assumed a 35 % dropout rate.

Variations in the endpoints between the baseline value and treatment assessment points will be compared between the groups, using a *t*-test or a Mann–Whitney U-test. The statistical tests are 2-sided, and the significance level is set at 0.05. The number of participants in the treatment and placebo groups who drop out due to disease progression will be analyzed using Kaplan − Meier curves and the log-rank test. Subgroup analysis (sex, and treatment with or without levodopa) will be performed.

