### Enrollment and data collection

One-hundred-and-seventy-eight Japanese participants with PD have already been enrolled in 14 hospitals and have been randomized, between April 1, 2013 and September 30, 2015, at their baseline visit. The participants will be followed-up for 80 weeks. The baseline characteristics are shown in Table 1. Despite extensive efforts to enroll more participants, the expected number of participants was not met, as it is difficult for some patients to consume 1000 mL water daily.

**Table 1 Tab1:** The baseline characteristics of the study participants

	Mean	Std. Deviation
Age	64.2	9.2
Disease duration	6.8	4.5
Sex (male/female) n	89	89
Wearing off (+/-) n	58	120
Dyskinesia (+/-) n	42	136
Levodopa mg	344.1	202.8
Levodopa (+/-) n	154	24
Dopamine agonist levodopa equivalent dose (mg) [12]	166.3	121.1
Total levodopa equivalent dose (mg) [12]^a^	592.0	317.6
Unified Parkinson’s Disease Rating Scale		
Part I	0.7	1.2
Part II	5.6	3.9
Part III	15.7	8.4
Part IV	1.7	2.2
Total	23.7	11.8
Modified Hoehn and Yahr stage	2.1	0.6
Parkinson’s disease Questionnaire-39		
Mobility	10.4	9.1
Activities of daily living	5.2	5.1
Emotional well-being	6.0	4.4
Stigma	3.2	2.8
Social support	1.4	1.9
Cognitions	4.0	3.0
Communication	1.7	2.2
Body discomfort	2.5	2.6
Total	34.4	24.2

^a^: not including istradefylline and zonisamide

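### Allocation was stratified by levodopa use but the log-rank test is named without strata; if hazards differ markedly by levodopa use, it is conservative and loses power on this secondary endpoint (minor)

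*Protocol article*

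**What the plan says.** All places are in the protocol article.

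- **Randomization and blinding:** participants were "assigned using a stratified randomization method according to their age and if they were receiving levodopa". The Methods section gives a 1:1 ratio.
- **Statistical analysis:** "The number of participants in the treatment and placebo groups who drop out due to disease progression will be analyzed using" Kaplan-"Meier curves and the log-rank test". No stratification factor is named. A subgroup analysis by sex and by levodopa use is planned, without saying for which endpoints.
- **Procedures (text below Fig. 1):** the duration endpoint is "the duration until the protocol is finished because additional levodopa is required or until the disease progresses".
- **Table 1:** "Levodopa (+/-) n 154 24". The abstract gives the same split.

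The article gives no event rate, number of events, hazard ratio or power for the time-to-event comparison.

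**The concern.** Levodopa use was important enough to stratify the allocation, so the arms are balanced within each levodopa group. A log-rank test that ignores the factor computes its variance as if that balance could have failed. When the event hazard differs between the groups, the variance is too large, the true type I error falls below 5%, and power is lost.

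A hazard difference is plausible here. Under the wording in Procedures, needing additional levodopa is naturally read as an increase for the 154 who already take it and as a first start for the 24 who do not. The article does not draw this distinction and does not say how often either would occur.

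At stake is power on a secondary endpoint that captures participants who leave the protocol because they worsen. No false positive is risked.

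**Working it through.** **1. Is there a figure in the plan to reproduce?** No. The sample size statement concerns the UPDRS difference only. The check is therefore a simulation under stated assumptions.

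**2. Inputs from the article.** 154 levodopa-treated and 24 levodopa-free participants, allocated 1:1 within each group (77 + 77 and 12 + 12); 72 weeks of treatment; two-sided alpha 0.05. The levodopa-free share is 24/178 = 13.5%.

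**3. Assumptions, not in the article.** Exponential event times; 15% independent dropout for other reasons; a 72-week placebo risk of 20% in levodopa-treated participants; a placebo risk of 20%, 40%, 60% or 80% in levodopa-free participants; and a treatment hazard ratio of 1 (null) or 0.5 in both groups.

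**4. Hazard ratio between the levodopa groups.** With constant hazards it is ln(1 − risk in levodopa-free) / ln(1 − risk in treated):

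- 40%: ln 0.6 / ln 0.8 = 0.511/0.223 = 2.3
- 60%: ln 0.4 / ln 0.8 = 0.916/0.223 = 4.1
- 80%: ln 0.2 / ln 0.8 = 1.609/0.223 = 7.2

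**5. The two tests.** Unstratified: Z = (O − E)/√V, with all 178 in one risk set. Stratified: Z = Σ(O_s − E_s)/√ΣV_s, with O, E and V computed within each levodopa group s and then summed. Each rejects when |Z| > 1.96.

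**6. Results** (6,000 simulated trials per setting):

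| Levodopa-free placebo risk | Type I error, unstratified / stratified | Power at HR 0.5, unstratified / stratified | Power lost |
|---|---|---|---|
| 20% | 5.3 / 5.4% | 39.2 / 39.0% | none |
| 40% | 4.7 / 4.9% | 41.9 / 42.7% | 0.8 points |
| 60% | 3.8 / 4.8% | 44.6 / 48.5% | 3.9 points |
| 80% | 2.8 / 5.2% | 42.8 / 54.1% | 11.3 points |

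The simulation standard error of a 5% rate is √(0.05 × 0.95/6000) = 0.3 points. Independent repeats of the three unequal settings gave unstratified type I errors of 4.8–4.9%, 3.7–4.0% and 2.9–3.0%, and power losses of 0.8–1.0, 3.7–3.8 and 10.9–11.4 points.

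**7. Other base risks** (20%, 35% or 50% in the treated, no other dropout, 40,000 trials per setting, HR 0.5 in both groups):

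| Levodopa-free hazard relative to treated | Unstratified type I error | Power gained by stratifying |
|---|---|---|
| 0.25 to 2 times, unequal | 4.3–4.9% | 0.2–1.3 points |
| 4 times | 3.6–4.0% | 3.9–5.6 points |
| 8 times | 2.5–3.0% | 12–16 points |

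The stratified test stayed at 4.8–5.2% throughout. The loss therefore becomes material only at about a fourfold difference.

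**8. When the effect differs between groups** (HR 0.5 in treated, 1 in levodopa-free, same design as step 7). Power, unstratified / stratified:

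| Base risk in treated | Hazard 2 times | Hazard 4 times |
|---|---|---|
| 20% | 28.9 / 28.6% | 24.6 / 25.2% |
| 35% | 49.6 / 47.8% | 46.6 / 44.3% |
| 50% | 68.9 / 65.6% | 67.4 / 63.3% |

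Here stratifying costs 0.3 to 3.3 points at a twofold hazard. At fourfold it ranges from a gain of 0.6 to a loss of 4.1 points.

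**9. The event.** Statistical analysis counts dropout due to disease progression. Procedures counts the end of the protocol because more levodopa is needed, or progression. The second is wider unless a need for levodopa is itself classed as progression, which the article does not say.

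**The case against.** The case for leaving this alone has five parts.

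- **Silence is not pooling.** A condensed article may leave the strata of a secondary test to the analysis plan, and an unseen plan may already stratify. This stands as far as it goes: pooling is the ordinary reading of an unqualified log-rank test, not something the article declares. The reason to raise it is that the article itself names the allocation factor and then a test that does not use it.
- **A reader might infer that the test must be conservative because starting and increasing levodopa are different events.** The documents do not support that. Conservatism comes from unequal hazards, not from different meanings, and no rates are given. Moreover, the log-rank sentence names progression only; the levodopa event comes from Procedures.
- **The visible losses need large differences.** This is correct. With 13.5% levodopa-free, up to a twofold difference is negligible, and nothing in the article establishes a fourfold one.
- **Stratifying is not always better.** This is also correct. The Background says the earlier positive trial was in levodopa-treated patients, so an absent effect in the other 24 cannot be excluded, and stratifying could then lose power.
- **The planned levodopa subgroup analysis may cover it.** Only in part. It may show separate curves, but about 12 per arm cannot carry a test, and separate analyses do not give one combined stratified result.

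**Conclusion.** The point holds in conditional form and is minor. Named without strata after levodopa-stratified allocation, the log-rank test is valid, but it is conservative if hazards differ by levodopa use.

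With an assumed 20% placebo risk in the treated, type I error is about 4.8%, 3.8% and 3% at levodopa-free risks of 40%, 60% and 80%. About 1, 4 and 11 points of power are lost at a hazard ratio of 0.5 common to both groups. At equal rates nothing is lost. These sizes rest on assumed event rates, exponential times and a common treatment effect, none of which the article provides.

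The mismatch between the two event descriptions needs no assumption: the passages must be reconciled. A reader might extend the point to the UPDRS comparison or to false-positive risk. Neither follows, since only the time-to-event analysis is concerned and any error is on the conservative side.

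**What to change.** 1. In Statistical analysis, state that the log-rank test, and any Cox model used for a hazard ratio, is stratified by levodopa use at baseline. If the unseen analysis plan already says so, it is enough to confirm it. Fix this before unblinding.
2. Use one event description in both Procedures and Statistical analysis, and say how it applies to participants not on levodopa at baseline. Which description is right is for the investigators.
3. Optionally, show Kaplan-Meier curves by levodopa group as description only.

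**Cost:** one sentence and one program option for item 1, since the factor is recorded and was used for allocation. The statistical price arises if treatment has no effect in levodopa-free participants: a loss of up to about 3 power points at a twofold hazard, and about 4 in the least favourable setting examined (fourfold hazard, 50% base risk). The stratified test kept its nominal level in every setting of step 7.

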### Enrollment and data collection

One-hundred-and-seventy-eight Japanese participants with PD have already been enrolled in 14 hospitals and have been randomized, between April 1, 2013 and September 30, 2015, at their baseline visit. The participants will be followed-up for 80 weeks. The baseline characteristics are shown in Table 1. Despite extensive efforts to enroll more participants, the expected number of participants was not met, as it is difficult for some patients to consume 1000 mL water daily.

**Table 1 Tab1:** The baseline characteristics of the study participants

	Mean	Std. Deviation
Age	64.2	9.2
Disease duration	6.8	4.5
Sex (male/female) n	89	89
Wearing off (+/-) n	58	120
Dyskinesia (+/-) n	42	136
Levodopa mg	344.1	202.8
Levodopa (+/-) n	154	24
Dopamine agonist levodopa equivalent dose (mg) [12]	166.3	121.1
Total levodopa equivalent dose (mg) [12]^a^	592.0	317.6
Unified Parkinson’s Disease Rating Scale		
Part I	0.7	1.2
Part II	5.6	3.9
Part III	15.7	8.4
Part IV	1.7	2.2
Total	23.7	11.8
Modified Hoehn and Yahr stage	2.1	0.6
Parkinson’s disease Questionnaire-39		
Mobility	10.4	9.1
Activities of daily living	5.2	5.1
Emotional well-being	6.0	4.4
Stigma	3.2	2.8
Social support	1.4	1.9
Cognitions	4.0	3.0
Communication	1.7	2.2
Body discomfort	2.5	2.6
Total	34.4	24.2

^a^: not including istradefylline and zonisamide

## Discussion

Fujita *et al.* have indicated that the intake of H_2_-water, even after MPTP administration, reduces neurotoxic damage [5]. The findings of our previous study [7] on PD patients are in agreement with the previous results that were obtained in animal models.

Antioxidant supplements that are considered medicinal products should undergo sufficient evaluation before marketing, as they might be harmful at high doses [9]. H_2_ selectively reduces •OH radicals, but not O_2_^**−**^•, H_2_O_2_, or NO• [4]. It is expected that prolonged application of H_2_ will have no or little adverse effects in chronic diseases. The effects of H_2_ could be mediated by modulating activities and expression of various molecules, such as Lyn, ERK, p38, JNK, ASK1, Akt, GTP-Rac1, iNOS, Nox1, NF-κB, p65, Iκba, STST3, NFATc1, c-Fos, and ghrelin [10]. Iuchi et al. proposed a hypothetical model in which H_2_ is linked to the modulation of Ca^2+^ signal transduction and the nuclear factor of activated T cells (NFAT) pathway via oxidized phospholipid species [11].

Our previous trial was the first randomized double-blind study of H_2_-water in patients with PD [7]. H_2_-water exhibited no adverse effects at a dose of 1000 mL/day in PD subjects receiving levodopa treatment. The results of the previous study will be confirmed in this longer and larger-scale study that includes patients who are not medicated with levodopa. This study will confirm the safety and tolerability of H_2_-water and if H_2_-water can improve PD symptoms.

## Ethics approval

A randomized double-blind multi-center trial of hydrogen water for Parkinson’s disease was approved by the Ethics Committee of the Juntendo University School of Medicine, and the ethics committees of other centers.

## Consent for publication

Not applicable.

## Availability of data and material

Not applicable.

## Abbreviations

CONSORT: Consolidated Standards of Reporting Trials
H_2_: hydrogen
H & Y: modified Hoehn and Yahr staging
MPTP: 1-methyl-4-phenyl-1,2,3,6-tetrahydropyridine
NFAT: nuclear factor of activated T cells
PD: Parkinson’s disease
PDQ-39: Parkinson’s disease Questionnaire-39
UPDRS: Unified Parkinson’s Disease Rating Scale
